## Abstract

**Introduction:**

There is controversy regarding the importance of air-transmitted infections for surgical site infections (SSIs) after orthopaedic surgery. Research has been hindered by both the inability in blinding the exposure, and by the need for recruiting large enough cohorts. The aim of this study is to investigate whether using a new form of air purifier using plasma air purification (PAP) in operating rooms (ORs) lowers the SSI rate or not.

**Methods and analysis:**

Multicentre, double-blind, cluster-randomised, placebo-controlled trial conducted at seven hospitals in 2017–2022. All patients that undergo orthopaedic surgery for minimum 30 min are included. Intervention group: patients operated in OR with PAP devices turned on. Control group: patients operated in OR with PAP devices turned off. Randomisation: each OR will be randomised in periods of 4 weeks, 6 weeks or 8 weeks to either have the devices on or off. Primary outcome: any SSI postoperatively defined as a composite endpoint of any of the following: use of isoxazolylpenicillin, clindamycin or rifampicin for 2 days or more, International Classification of Diseases codes or Nordic Medico-Statistical Committee codes indicating postoperative infection. In a second step, we will perform a chart review on those patients with positive indicators of SSI to further validate the outcome. Secondary outcomes are described in the Methods section. Power: we assume an SSI rate of 2%, an SSI reduction rate of 25% and we need approximately 45 000 patients to attain a power of 80% at a significance level of 0.05.

**Ethics and dissemination:**

The study is approved by the Swedish Ethical Review Authority. The interim analysis results from the study will be presented only to the researchers involved unless the study thereafter is interrupted for whatever reason. Publication in a medical journal will be presented after inclusion of the last patient.

**Trial registration number:**

NCT02695368.

Strengths and limitations of this studyEPOS is a multicentre, placebo-controlled trial with approximately 45 000 study subjects, that will evaluate the effect of plasma air purification on the incidence of surgical site infections (SSIs) after orthopaedic surgery.The double-blinded design provides strong internal validity to the study results.The cluster-randomisation design, which is created through switching of the exposure within each operating room (OR), minimises the risk of allocation bias.This study is the first randomized controlled trial, to the best of our knowledge, investigating the true cause-and-effect relationship between an air-purifying intervention in ORs and SSIs.The primary limitation to the study is the resource intensity, mainly due to the large number of study subjects required to study such an unusual outcome, and the concomitant review of medical records to validate the outcome.

## Introduction

Despite surgery in clean operating rooms (ORs), surface sterilisation and antibiotics, SSI after orthopaedic surgery have an overall estimated incidence of 1%–4%.^1–3^ This feared complication is associated with long-term antibiotics, repeated surgeries, prolonged hospital stays, economic burden and a poorer end result for individual patients.^4 5^ Prevention of SSIs is, therefore, of paramount importance.

Air flow within the OR can spread airborne particles, posing a potential risk for postoperative infection. These airborne particles include dust, textile fibres, skin scales and respiratory aerosols, loaded with viable microorganisms (including *Staphylococcus aureus*) having been released mainly from the surgical team members and patient into the surrounding air of the OR. These particles have been shown to settle onto surfaces, including the surgical wound and instruments.^6^ Thus, air-transmitted infections is one of the main reasons for SSI,^6^ making this an interesting intervention target.

Ever since the ground-breaking study by Charnley and Eftekhar,^7^ which showed that cleaner air in the OR drastically improved infection rates after total hip arthroplasty, vast efforts have been made to address this issue. Lidwell *et al* carried on their work, showing that ultra-clean air (ie, <10 colony-forming units (CFUs)/m^3^) in combination with body-exhaust suits and prophylactic antibiotics further improved infection rates.^8–10^ Based on their work, in combination with several reports showing that laminar air flow (LAF) reduces bacterial contamination in the OR air,^11–13^ many ORs are today equipped with LAF ventilation. Unfortunately, though, when evaluated in large cohort studies, systematic reviews and meta-analyses, LAF systems in modern state-of-the-art ORs have so far failed to prove efficient in preventing infections, compared with conventional ventilation.^14–19^

The plasma air purification (PAP) system used in our current study is an air purifier that sterilises the air particles through a plasma chamber (figure 1). Air in the OR is pumped through the chamber, and by using a small current, it transforms the air in the vicinity of the electrode into plasma, which eradicates any bacteria that pass through (figure 2). The small size of the machine allows it to fit into any operating theatre without interfering with existing equipment.^20^

**Figure 1 F1:**
[figure not shown]
Rendered view of Novaerus NV800.

**Figure 2 F2:**
[figure not shown]
Air flow through the air purifier.

Similar systems exists that use ultraviolet light to sterilise air particles and reduce the rate of hospital-acquired infections.^21 22^ There are though few peer-reviewed articles regarding air purification. While we have not found any randomised clinical trials, there are randomised field trials, outside hospital settings, that have shown positive effects in vivo. In a blinded randomised field trial on healthy volunteers using air purifiers, a significant reduction in air particles were seen and this also led to a reduction of stress hormone for the participants.^23^

In hospital and OR settings, the PAP technology alone significantly reduces the number of CFUs of *Staphylococci* (the most common infecting microorganism in SSI) from 49% to 97%.^24^ In non-randomised studies, it has been shown to reduce respiratory infections, personnel sick leave and severe infectious outbreaks.^22 24^ These effects have though not been validated in randomised clinical trials in OR settings. However, this is also true for all methods of reducing airborne pathogens in ORs that currently are used, such as surgery in LAF ORs. The need for Level 1 evidence in this field of medicine is urgent.

The EPOS trial is, therefore, designed as a multicentre, double-blinded, cluster-randomised, placebo-controlled trial.

The aim of this study is to investigate whether using PAP devices that clean the air from contaminating particles in ORs lower the rate of SSI, or not. The primary endpoint will be SSI rate within 12 weeks postoperatively, defined as either use of antibiotics targeting common implant pathogens, International Classification of Diseases (ICD) code or Nordic Medico-Statistical Committee (NOMESCO) code indicating postoperative infection. This proxy variable is more closely described in the Methods section. We hypothesise that PAP can reduce the incidence of SSI in orthopaedic surgery by 25%. Secondary aims include investigating the number of prescribed antibiotics as well as the number of needed readmissions and length of stay for SSI.

## Methods: participants, interventions and outcomes

### Study setting

The study is being conducted at seven major hospitals in Sweden (table 1). Inclusion will take place between April 2017 and 31 December 2021. The randomised clinical trial setting has been chosen to control for the huge number of possible confounders influencing the outcome. The study protocol has been written according to the Standard Protocol Items: Recommendations for Interventional Trials statement. A Consolidated Standards of Reporting Trials flow diagram, published as an online supplemental file 1 to this protocol, describes our study graphically.

10.1136/bmjopen-2020-047500.supp3Supplementary data

**Table 1 T1:** Recruitment centres and estimated recruitment based on number of surgeries performed annually. The hospitals are already recruiting patients

Centre	Estimated n	% recruited
Danderyd Hospital	8000	18%
Hässleholm/Kristianstad	10 000	22%
Huddinge Hospital	6000	13%
Akademiska Hospital	10 000	22%
Ortho Centre	3000	7%
Umeå	8000	18%
Total sample size	45 000	100%

### Eligibility criteria

We will include^1^ all patients that undergo surgery for 30 min or longer at each centre during the study period. We assume that surgeries lasting less than 30 min are less susceptible to SSIs. Including those in this study would, therefore, result in a larger cohort. We will exclude surgeries on (1) already infected surgical sites, defined as: ICD or NOMESCO codes indicating infection (same as those used for the primary outcome, see below), open fractures, traumatic wounds and vacuum-assisted wound therapy, (2) patients that have withdrawn antibiotics 2 weeks or less prior to surgery and (3) patients that have actively marked their hospital charts with an added privacy notice. If patients have multiple surgeries during the study period, only the first operation will be included.

### Intervention

At each hospital, all ORs that perform surgery on orthopaedic patients will be equipped with three^3^ PAP systems each. The groups are defined as: intervention group: those operated where the PAP device has been turned on for at least 2 days prior to index surgery; control group: those where the PAP device has been turned off for at least 2 days prior to index surgery; and mixed group: those receiving surgeries in ORs within 2 days after the PAP device switches status. In the analysis we will also subgroup the study subjects according to measurements prior to study start into regular ORs (≥10 CFU/m^3^) and ultra-clean ORs (<10 CFU/m^3^).

PAP device status and function will be monitored continuously during the inclusion period through standardised manual controls every 3 months, and also at the end of the inclusion period by validating PAP device status retrospectively through memory card recordings in each device.

### Outcomes

The primary outcome is any indication of SSI within 12 weeks postoperatively, defined as a composite endpoint of any of the following:

Withdrawal or other documented use of antibiotics corresponding to 2 days or more after surgery targeting *S. aureus*.ICD code indicating postoperative infection (at date of readmission)NOMESCO code indicating postoperative infection.

In a second step, we will perform a chart review on those patients with positive indicators of SSI to further validate the outcome. We will use the internationally accepted CDC definition of SSI when finally establishing that an SSI has occurred (box 1).^25^

Box 1CDC definition of SSISuperficial incisional SSIInfection within 30 days after the operation and only involves skin and subcutaneous tissue of the incision and at least one of the following:Purulent drainage with or without laboratory confirmation, from the superficial incision.Organisms isolated from an aseptically obtained culture of fluid or tissue from the superficial incision.At least one of the following signs or symptoms of infection: pain or tenderness, localised swelling, redness or heat, and superficial incision is deliberately opened by surgeon, unless incision is culture-negative.Diagnosis of superficial incisional SSI made by a surgeon or attending physician.Deep incisional SSIInfection occurs within 30 days after the operation if no implant is left in place or within 1 year if implant is in place and the infection appears to be related to the operation and infection involves deep soft tissue (eg, fascia and muscle) of the incision and at least one of the following:Purulent drainage from the deep incision but not from the organ/space component of the surgical site.A deep incision spontaneously dehisces or is deliberately opened by a surgeon when the patient has at least one of the following signs or symptoms: fever (>38°C), localised pain or tenderness, unless incision is culture-negative.An abscess or other evidence of infection involving the deep incision is found on direct examination, during reoperation, or by histopathologic or radiologic examination.Diagnosis of deep incisional SSI made by a surgeon or attending physician.Organ/space SSIInfection occurs within 30 days after the operation if no implant is left in place or within 1 year if implant is in place and the infection appears to be related to the operation and infection involves any part of the anatomy (eg, organs and spaces) other than the incision, which was opened or manipulated during an operation and at least one of the following:Purulent drainage from a drain that is placed through a stab wound into the organ/space.Organisms isolated from an aseptically obtained culture of fluid or tissue in the organ/space.An abscess or other evidence of infection involving the organ/space that is found on direct examination, during reoperation, or by histopathologic or radiologic examination.Diagnosis of organ/space SSI made by a surgeon or attending physician.SSI, surgical site infection.

The effect size of the primary endpoint is the relative risk of contracting SSI for the intervention group versus the control group and will be calculated by dividing the probability of contracting an SSI in the intervention group by the control group=$\frac{SSIrateinterventiongroup}{SSIratecontrolgroup}$. The effect size will also be presented as an absolute risk difference=SSIrateinterventiongroup−SSIratecontrolgroup.

The primary outcome is a surrogate variable for SSI as it, due to the large sample size, is practically impossible to have all patients come back for outpatient visits and be visually inspected. To further validate the outcome, a medical record review will be performed in a second step on all individual patients with indication of SSI. Our expectations are that the choice and succeeding validation of this proxy variable can provide us with a reliable tool for investigating SSI’s in future projects.

The Swedish healthcare registers, especially the Prescribed Drug Register (PDR) and the Patient Register, will make sure that we get an almost complete (>99%) coverage of all relevant SSIs.

The secondary outcomes are: (1) withdrawal or other documented use of any antibiotics for 2 days or more after surgery during the first 30 postoperative days, (2) the number of days with antibiotics during the first 30 days, (3) same as (1) and (2) but up to 90 days after surgery and (d) death during the first 2 postoperative years

These analyses will also be performed with and without adjustment for preoperative antibiotic use 6 months prior to the surgery.

### Sample size

The reoperation rate in Sweden due to infections within the first 2 years after surgery is 1.3%^3^ for primary total hip replacements (THRs). This does not include THRs in patients with fracture and other types of surgeries that are more susceptible to infections. We, therefore, assume that the SSI rate in our study population is 2%.^1–3^ Similarly, we know from other data that about 0.7% withdraw the antibiotics associated with the primary outcome within a 3-month period prior to surgery. To account for infections unrelated to surgery, we assume that the infection noise rate, that is, non-SSIs, is less than 2%.

#### Multicentre power with ultra-clean air

Hospitals with ORs with ultra-clean air may be less susceptible to the effect with an already lower infection rate. Pre-study CFU measurements suggest that approximately 80% of the included ORs are ultra clean. If we assume that the infection rate is 2% or less, and that the effect size is reduced to 25% in an ultra-clean environment, we will need to recruit 22 630 patients in each group, that is, approximately 45 000 patients to attain a power of 80% with a significance level of 0.05. This will be our target population. We expect a very low drop-out rate/missing data in the study, estimated to be <1%. At the interim analysis, the p value will be set 10 times lower at 0.005, that is, if a statistically significant result between the groups is observed at 18 months, the study will be stopped. See figure 3 and online supplemental appendix 1 for details in R and explanation of the script for the sample size analysis.

10.1136/bmjopen-2020-047500.supp1Supplementary data

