### Statistical methods

The primary outcome is a binary variable where there are three groups. We will use logistic regression where the reference group is the placebo group, and the significance is related to the intervention group. The estimate for the mixed group is only for relating dose effect, that is, the group will not be pooled with either the placebo or the intervention group. Due to the randomisation, we do not intend to have any other covariates as confounders in the model. Similar methodology will be applied to the antibiotic’s binary outcome. The number of days with antibiotics will be modelled using a linear regression with the similar interpretation to above regarding predictors. Mortality will be modelled using a Cox proportional hazards model with time since surgery calculated as time to death, migration or 2 years. The Cox model will not contain any covariates due to the randomised study nature. The analysis will be performed by an epidemiologist/statistician in our team (MG) and will be performed as a per-protocol analysis.

We will handle confounding by including only the patient’s first surgical procedure. The randomisation process will handle other confounding such as confounding by selection. Procedural confounding will be handled by the external part who has done the randomisation procedure for each PAP device. Regarding dropouts, the healthcare registers and chart review done in the study will ensure a very low (<1%) drop-out rate. Individual patients can also request that they are excluded from the registers and thus from the study, but by experience, this is very rare and will also not affect our ability to analyse our primary and secondary endpoints.

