## Methods: monitoring

### Data monitoring

At 12 months after study start (17 April 2018), an interim analysis will be performed and the recruitment rate from each centre will be evaluated. The study recruitment will end once we have reached a minimum of 45 000 patients. During the second half of 2017/early 2018, the data quality of each recruiting centre will be evaluated by extracting data from each centre’s hospital information centre.

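### The stated 80% power is for an individually randomised trial at exactly 2% SSI plus 2% noise; it allows nothing for clustering or the mixed group, and the wording on the SSI rate points the wrong way

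*Protocol article*

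**What the plan says.** The Sample size section starts from an SSI rate: "We, therefore, assume that the SSI rate in our study population is 2"%. It then adds an allowance for infections unrelated to surgery, put at less than 2%; its one supporting figure is that about 0.7% of patients collect the relevant antibiotics in a 3-month period before surgery.

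The subsection on multicentre power with ultra-clean air restates the premise as "If we assume that the infection rate is 2% or less, and that the effect size is reduced to 25% in an ultra-clean environment" and concludes that 22 630 patients per group are needed "to attain a power of 80% with a significance level of 0.05". Drop-out is expected to be below 1%. The Abstract gives the headline form: "we assume an SSI rate of 2%, an SSI reduction rate of 25"%, with about 45 000 patients.

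Three features of the design bear on this figure:

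- Allocation: each operating room (OR) is randomised to on or off in periods of 4, 6 or 8 weeks.
- Statistical methods: patients operated on within 2 days of a switch form a mixed group, and "the group will not be pooled with either the placebo or the intervention group".
- Data monitoring: "The study recruitment will end once we have reached a minimum of" 45 000 patients.

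**The concern.** A reader takes 80% power as a property of the trial as designed, holding for any SSI rate up to 2%. Neither part follows. The calculation appears to treat patients as independently randomised and all of them as contributing to the on-off comparison. And an upper bound on the event rate is the wrong kind of condition: with a fixed relative reduction, a lower rate means a smaller absolute difference and less power. The same paragraph says that hospitals with ultra-clean rooms, about 80% of the rooms, may already have a lower infection rate.

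At stake is how a null result is read. It could be presented as having had 80% power against a 25% reduction when, under the article's own sizing inputs, the figure is lower.

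**Working it through.** **Inputs.** Alpha 0.05 and power 80% (power subsection; sidedness not stated). SSI rate 2% and noise below 2% (Sample size). Relative reduction 25% (Introduction, Abstract). Noise is added to both arms and is unaffected by the device.

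**Step 1: reproduce 22 630.** For two proportions, 1:1, with p̄ = (p1 + p2)/2:

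n = [z(0.975)·√(2p̄(1−p̄)) + z(0.80)·√(p1(1−p1) + p2(1−p2))]² / (p1 − p2)²

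- SSI only, 2.0% v 1.5%: n = 10 795 per group. Does not reproduce.
- SSI plus 2% noise, 4.0% v 3.5%: n = (0.5266 + 0.2261)² / 0.005² = 22 662. The arcsine version gives 22 639. Both reproduce.
- The same rates one-sided: 17 852. Does not reproduce.

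So 22 630 is the two-sided 4.0% v 3.5% figure with a design effect of 1, and it leaves no room for any inflation.

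**Step 2: vary the SSI rate and the noise.** Control rate = SSI + noise; intervention rate = 0.75 × SSI + noise. Power at 22 630 per group, no clustering, nobody set aside:

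| SSI rate | noise 0.7% | noise 1% | noise 1.5% | noise 2% |
|---|---|---|---|---|
| 2.0% | 93% | 90% | 85% | 80% |
| 1.8% | 89% | 86% | 79% | 73% |
| 1.5% | 81% | 76% | 67% | 61% |

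In every column power falls as the SSI rate falls, so 2% is the best case in the stated range. At 1.5% SSI and 2% noise, 80% power would need 35 751 per group.

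**Step 3: total, drop-out and mixed group (2% SSI, 2% noise).**

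- 2 × 22 630 = 45 260. Stopping at 45 000 (22 500 per arm) gives 79.7%, against 79.9% at 22 630.
- A further 1% lost gives 79.3%.
- The mixed group's calendar share is at most 2/56 to 2/28 days, that is 3.6% to 7.1%, which alone gives 78.3% to 76.7%. Switching at midnight on Friday puts those days on the weekend; a share of 1–2% gives about 79%.

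**Step 4: clustering.** Design effect = 1 + (m − 1) × net ICC, with m patients per OR-period. The article gives neither m nor an ICC, so these are assumptions. With m = 75 and 22 500 per arm, at 2% SSI and 2% noise:

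- net ICC 0.0005: design effect 1.037, power 78.3%
- net ICC 0.001: design effect 1.074, power 76.8%
- net ICC 0.005: design effect 1.37, power 66.5%

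**Step 5: the losses together, at 2% SSI.** Per-arm n = 22 500 × 0.99 × (1 − mixed share) / design effect:

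| Mixed share, design effect (assumed) | effective n per arm | noise 0.7% | noise 1% | noise 2% |
|---|---|---|---|---|
| 1%, 1.05 | 21 002 | 91% | 88% | 77% |
| 3%, 1.10 | 19 642 | 89% | 86% | 74% |
| 5%, 1.20 | 17 634 | 86% | 82% | 70% |

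**Step 6: room for a design effect at 2% SSI.** 22 630 / 16 792 = 1.35 at 1% noise; 22 630 / 15 006 = 1.51 at 0.7% noise. At 1.5% SSI and 0.7% noise the room is only 22 630 / 22 012 = 1.03.

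**The case against.** The strongest reply is that the noise ceiling is a cautious input. The article says noise is less than 2%, and its only data point is 0.7%. At 2% SSI and 1% noise, even the heaviest combined loss in Step 5 leaves 82%. This stands, and it makes the shortfall conditional. It is not complete cover: the 0.7% counts antibiotics only, while the endpoint also includes diagnosis and procedure codes, and the reserve nearly disappears at 1.5% SSI. Nor does low noise correct the wording about the SSI rate.

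A second reply concerns clustering. With no ICC or period size in the article, the loss cannot be quantified, and because each room crosses between on and off, part of the between-room correlation cancels. The loss may be small. That also stands; what remains is that the stated figure contains no allowance at all.

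Four stronger readings are tempting, and the document does not support them:

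- **That true power is about 70–77%.** This holds only at 2% noise with an assumed design effect of 1.05–1.2.
- **That 1.3% is the likely SSI rate.** The article gives it as a 2-year reoperation rate for infection after primary hip replacement and explains why its wider case mix should have more infections.
- **That the Abstract is wrong because its inputs alone give about 21 600 patients.** The noise term is stated in the Sample size section; an abstract condenses.
- **That stopping at 45 000 rather than 45 260 matters.** It costs 0.2 percentage points, and 45 000 is described as approximate and as a minimum.

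Finally, Figure 3 (not shown) is captioned as displaying required sample size against SSI rate and unrelated infections, so that sensitivity was not ignored. The text still states an unconditional 80%.

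**Conclusion.** The point holds in a limited form. As stated, 80% power belongs to an individually randomised comparison at 4.0% v 3.5% in which every patient counts. It is not shown for a trial randomised by OR-period with a mixed group set aside, and over SSI rates up to 2% it is a maximum, falling to 73% at 1.8% and 61% at 1.5% if noise is at its 2% ceiling.

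Whether the trial falls short in fact depends on noise, SSI rate and net ICC, none of which the article fixes. If SSI is 2% and noise is 1% or less, there is room for the mixed group and a modest design effect. If noise is at the ceiling there is no slack, and every loss takes power below 80%. These results assume a 25% relative reduction in SSI, noise equal in both arms, and a two-sided test. The mixed-group and drop-out losses are minor; the SSI-rate wording and the absent cluster allowance are the substance.

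**What to change.** Amend the power paragraph:

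1. State the inputs that give 22 630: 4.0% v 3.5%, two-sided, made up of 2% SSI (1.5% with the device) plus 2% noise.
2. Replace "If we assume that the infection rate is 2% or less" by an SSI rate of 2%, or of at least 2%.
3. Give power for the patients who enter the on-off comparison, after the mixed group and losses, over a range of SSI rate (for example 1.5–2%), noise (0.7–2%) and design effect. State the ICC and OR-period size as assumptions, and allow for the crossover within rooms.
4. Do not put a single lower figure in place of 80%.

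The cost is a rewritten paragraph and no new patients. The downside is that the stated power becomes conditional, and less favourable at the noise ceiling.

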## Methods: an assignment of interventions

### Allocation

The three PAP devices in each OR will synchronically be randomised in periods of 4 weeks, 6 weeks or 8 weeks to either have the system ‘on’ or ‘off’. The switch will always occur midnight Friday in order to limit the patients exposed to partial effect during the first 2 days after switching status. The system can be programmed to be active (ie, plasma chamber eradicating bacteria) at any given timeframe. The manufacturer of the PAP devices will prepare the randomisation allocation and automatic execution of it. The randomisation sequence is at minimum 8 years long and will be submitted to a third, independent party, responsible for keeping the allocation secret until interim analyses or study end. At the interim analyses, only allocations up to that date will be released.

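### The interim look that can stop the trial is dated 18 months in one section and 12 months in another, and 0.005 followed by an unreduced 0.05 gives an overall error above 5%

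*Protocol article*

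**What the plan says.** Three sections of the protocol article bear on the interim.

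- **Sample size, Multicentre power with ultra-clean air.** The trial needs 22 630 patients per group "to attain a power of 80% with a significance level of 0.05". The interim p value is set ten times lower, at 0.005, and "if a statistically significant result between the groups is observed at 18 months, the study will be stopped".
- **Data monitoring.** "At 12 months after study start (17 April 2018), an interim analysis will be performed", together with a review of each centre's recruitment. No threshold or stopping rule is given here.
- **Allocation.** "At the interim analyses, only allocations up to that date will be released". The noun is plural, but a single date is meant.

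The Ethics and dissemination section adds that interim results stay with the researchers unless the study is interrupted for a significant difference in infection rate between the groups. The Statistical methods section gives no threshold for the final test, and no section gives a reduced final level or an alpha-spending rule.

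**The concern.** There are two linked problems.

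**Timing.** A comparative look with the power to stop the trial needs one trigger fixed in advance. Here there are two candidates six months apart. A reader cannot tell whether one look is planned with its date misstated in one place, or two looks are planned. Whoever performs the look could point to either date, and that choice should not be open once data are available.

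**Error rate.** If 0.005 is spent at an interim and the final test is still judged at 0.05, the chance of a false positive over the whole trial exceeds 0.05. A final p value just under 0.05 would then be claimed at a level that the design does not hold.

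**Working it through.** **Inputs from the protocol article**

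- SSI rate 2%, and noise from unrelated infections below 2% (Sample size); 2% is used as the upper bound.
- 25% relative reduction, 22 630 per group, 80% power, level 0.05, interim level 0.005 (Multicentre power with ultra-clean air).
- Inclusion April 2017 to 31 December 2021, about 57 months (Study setting).
- Interim at 12 months (Data monitoring) or 18 months (Multicentre power with ultra-clean air).

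**Assumptions:** two-sided testing (not stated); even accrual; independent patients, so that clustering by operating room and period is ignored.

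**Step 1. Reproduce the stated sample size.** SSI falls from 2.0% to 1.5%; adding 2% noise to each arm gives p₁ = 0.040 and p₂ = 0.035, with mean 0.0375.

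n = [z₀.₉₇₅ √(2 × 0.0375 × 0.9625) + z₀.₈₀ √(0.040 × 0.960 + 0.035 × 0.965)]² / 0.005²

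= [1.960 √0.0721875 + 0.842 √0.072175]² / 0.000025 ≈ 22 663 per group.

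The stated figure is 22 630, a difference of 0.15%. A one-sided 0.05 test would need only 17 852. The plan's size is therefore a single-look, two-sided 0.05 design with no alpha reserved for the interim.

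**Step 2. Information fraction.** t = 12/57 = 0.21 or t = 18/57 = 0.32.

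**Step 3. Overall type I error.** Under the null, the interim statistic Z₁ and final statistic Z₂ are bivariate normal with correlation √t. The null is rejected if |Z₁| > 2.807 (p < 0.005) or |Z₂| > 1.960 (p < 0.05):

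α = 1 − P(|Z₁| ≤ 2.807 and |Z₂| ≤ 1.960).

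The corrected final level is the value that brings α back to 0.05. Power counts rejections at either look, at 22 630 per group.

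| Interim | t | Overall α, final 0.05 | Final level for 5% overall | Power, final 0.05 | Power, corrected |
|---|---|---|---|---|---|
| Early bound | 0.10 | 5.42% | 0.0457 | 80.1% | 79.0% |
| 12 months | 0.21 | 5.36% | 0.0463 | 80.1% | 79.2% |
| 18 months | 0.32 | 5.30% | 0.0469 | 80.1% | 79.4% |
| Halfway | 0.50 | 5.19% | 0.0481 | 80.1% | 79.7% |
| Late bound | 0.75 | 5.05% | 0.0495 | 80.0% | 79.9% |

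Rounding t to 0.32 before solving gives 0.0470 for the 18-month look. If looks are taken at both 12 and 18 months at 0.005 each, with a final test at 0.05, the overall error is about 5.57%.

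**Step 4. Allow for the 12-week outcome window.** Counting only patients whose window has elapsed lowers t to about 0.16 or 0.27. The overall error becomes 5.39% or 5.33%, and the corrected final level 0.0460 or 0.0466.

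**Step 5. Chance of stopping under the design effect.** The expected final Z is 0.005 / √(0.072175 / 22 630) = 2.80. The chance of crossing 2.807 at the interim is Φ(2.80√t − 2.807), which is about 6% at 12 months and 11% at 18 months.

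**The case against.** The date conflict is hard to contest; the objections are to the rest.

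- **The final level of 0.05 is inferred.** The document never says that the final test is at 0.05, and an analysis plan that is not shown might set another level. This is true as to wording. But the document names 0.05 as its significance level, describes the interim as ten times lower, and has a sample size that reproduces at an unreduced 0.05. The inference is sound.
- **The 12-month look may be operational.** The Data monitoring section pairs it with recruitment and attaches no test. That reading is possible but unlikely: the section lists the interim analysis in addition to the recruitment review, and other sections describe interim looks as releasing allocations and able to interrupt the study. If it is what was meant, the protocol needs to say so.
- **Two comparative looks are weakly supported.** The case rests mainly on one plural; the other sections use the singular. This stands: one look with a misstated date is the more natural reading, and 5.57% is an upper scenario.
- **The excess is small, and the figures depend on accrual.** Both points stand. The excess is 0.3 to 0.4 percentage points for one look at either stated date. Accrual and the outcome window move the figures slightly but do not change the direction.
- **The ambiguity is between two fixed points, not open-ended.** Fair, but a choice between two dates is still a choice that should be closed beforehand.

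**Conclusion.** The concern holds on both counts. The 12-month and 18-month statements contradict each other in current methods text, and that matters more than the arithmetic because it leaves a trial-stopping look without a single trigger. The error-rate point is correct but modest: about 5.36% or 5.30% against a stated 5% for one look, and above 5% at every timing checked from t = 0.10 to t = 0.75. It rests on a final two-sided test at 0.05, inferred as described, and on independent patients, as in the plan's own calculation. The exact size also depends on even accrual; the direction does not. This should be corrected, but it does not threaten the design as a whole.

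**What to change.** 1. State one interim look in both the sample-size and Data monitoring sections, triggered by one date or one patient count and limited to patients whose 12-week outcome window has elapsed. Use the singular in the Allocation section to match. If one of the two dates is purely operational, say so and state that no allocations are released for it.
2. Keep 0.005 at the interim and set the final level explicitly: about 0.046–0.047 for a look at 12 or 18 months, recalculated from the actual information fraction, or use a named spending function.
3. If comparative looks took place at both dates, report them and spend alpha for both. With 0.005 at each, solving as in step 3 of the working gives a final level of about 0.044.
4. Restate the power at the chosen final level.

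The cost is wording in these sections and a slightly stricter final threshold. At 22 630 per group, power falls from about 80.1% to 79.2% (12 months) or 79.4% (18 months). Holding 80% at those final levels, on a single-look calculation, would take about 23 190 or 23 100 per group.
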